## 2. Materials and Methods

### 2.1. Participants

A total of 54 professional male and female athletes aged 18–25 years will be recruited from collaborating sports clubs located in the Attica region of Greece. Eligible participants will be athletes participating in open-skill sports, including football, basketball, volleyball, and handball, who have sustained at least one chronic lower-limb musculoskeletal injury lasting more than three months. Recruitment will be conducted in collaboration with team coaches and sports medicine professionals affiliated with these clubs. Participants will be randomly assigned in a 1:1:1 ratio to one of three groups: the experimental group, the placebo group, or the control group (*n* = 18 per group). Randomization will be performed using a computer-generated random allocation sequence by an independent researcher who is not involved in participant recruitment, outcome assessment, or statistical analysis. Allocation concealment will be ensured using sequentially numbered, opaque, sealed envelopes. Participants, outcome assessors, and statisticians will remain blinded to group allocation throughout the study.

Sample size was calculated using G*Power software (version 3.1.9.7; Heinrich Heine University Düsseldorf, Düsseldorf, Germany) [47]. The calculation was based on a mixed-design repeated-measures ANOVA with three groups (experimental, placebo, and control) and three measurement time points (baseline, post-intervention, and four-week follow-up). Assuming a medium effect size (f = 0.25), an alpha level of 0.05, statistical power of 0.95 and equal allocation across groups, the minimum required sample size was estimated at 48 participants. To account for an anticipated dropout rate of approximately 10%, the final target sample size was set at 54 participants, with 18 participants allocated to each group. A medium effect size of Cohen’s f = 0.25 was selected as a realistic estimate for a non-invasive psychophysiological intervention (BB) targeting psychological and Performance outcomes. This estimate was considered appropriate because previous intervention studies examining kinesiophobia and rehabilitation-related outcomes in athletes with lower-limb injuries have reported comparable sample sizes (33–51 athletes) and medium effect estimates (0.25–0.40) [48,49,50].

To qualify for the study, participants must be diagnosed with at least one musculoskeletal injury (≥3 months) by a sports medicine doctor with at least 5 years of experience and their injury must have been repaired. Athletes must be active members of their respective team with a frequency of engaging in sports 3–5 times per week, including both training sessions and competitions. Additionally, they must be referred to as having kinesiophobia with TSK scores ranging from 17 to 37. Exclusion criteria encompassed hearing impairments, recent lower-limb injuries, recent surgery or a history of concussion. All inclusion and exclusion criteria for athletes to be recruited in the study are described in Table 1.

All measurements will be conducted at the Laboratory of Sports Excellence, the Orthopedic Research & Education Center of the University General Hospital “ATTIKON. Ethical approval was granted by the University of West Attica’s Ethics Committee (Approval No. 62664), adhering to the Declaration of Helsinki, and all participants will provide written informed consent before enrolment. Additionally, the protocol of this study was registered in the www.clinicaltrials.gov database (accessed on 17 January 2026) under identifier NCT07370636.

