### 2.2. Procedures

This double-blind randomized controlled trial will investigate the effects of binaural beats on biopsychological outcomes in professional athletes with a history of chronic lower-limb musculoskeletal injuries. The study will be conducted in three phases: baseline (pre-intervention), immediately after the four-week intervention, and four weeks after completion of the intervention. Outcome measures will include self-report questionnaires assessing kinesiophobia, sport-related anxiety, and pain beliefs; physiological assessments of autonomic nervous system (ANS) function; handgrip strength; and fitness-related biomarkers, including maximal oxygen uptake (VO_2_max), blood lactate concentration, and heart rate variability (HRV). All athletes will complete a four-week standardized binaural beats music-based intervention incorporated into the warm-up phase prior to each training session and official game. The BB intervention will be administered 5 times per week (pre-training and pre-game), resulting in a total of 20 sessions. Each session will consist of 15 min of music listening (Figure 1).

Prior to initiating the intervention, athletes will receive detailed oral and written information regarding the study aims and assessment procedures from licensed physiotherapists with five years of clinical research experience. Data collection will include both subjective and objective measures and will be conducted at three time points: baseline (pre-intervention), immediately post-intervention, and four weeks after the completion of the intervention. Written informed consent will be obtained from all participants before enrollment.

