### 2.4. Intervention: The Binaural Beats Intervention Program

BB is delivered through an auditory stimulus waveform that is interpreted as a brainwave pattern by the Reticular Activating System (RAS). The RAS regulates arousal, kinesiophobia, attention, and awareness—key elements of consciousness itself [73,74]. In this study, BB is layered with background music and will be provided in MP3 format following specific guidance, in the English language, based on fearless motion. All stimuli will be presented binaurally at High Beta and Gamma frequencies, via an auditory system incorporating headphones [75]. In fact, the purpose of High Beta and Gamma frequencies on athletes is to improve the athlete’s psychomotor and self-regulation ability, their confidence, and subsequent performance in important competitions [76]. The Binaural Beats (BB) intervention program will be designed and produced by the Monroe Institute (Faber, VA, USA).

This BB music-based intervention will be received in high beta and gamma frequencies (30–100 Hertz) at 30 bpm (slow tempo), 60 bpm (normal tempo), and 100 bpm (fast tempo). The binaural beat stimuli will consist of mixed sinusoidal tones producing frequency patterns will crop in length to a duration of six times intervals (total 15 min): 0–2 min the slow tempo (Grounding), 3 min (2–5 min) the slow tempo (Relaxation/Intention Setting), 3 min (5–8 min) the normal tempo (Imagery Begins), 2.5 min (8–10.5 min) normal tempo (Emotional Processing + Imagery/Movement), 2.5 min (10.5–13 min) fast tempo (Active Visualization + Affirmation), and 2 min (13–16 min) fast tempo (Return to Awareness, Light Activation) enabling athletes to hear the music; this duration will also be likely to yield more pronounced emotional response [77].

The intensity will be modified at approximately the isochrone tones to 14–16 dB.

Each athlete will receive the musical intervention via the website binaukine.com, which has been specifically designed by the researchers exclusively for the purposes of the present study. Furthermore, participants’ compliance with the study protocol will be monitored by the researchers through the frequency of the athletes’ visits to the website.

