The BB music-based intervention will be performed prior to each training session or competition, as part of the athletes’ warm-up routine. Athletes will be instructed to conduct the listening sessions in a quiet environment, seated comfortably with their eyes closed, and to avoid distractions from external stimuli during the intervention. All groups will receive the BB music-based interventions for 20 sessions, lasting 15 min per session, 5 times per week, over a period of 4 weeks.

Before beginning the BB music-based intervention phase, all athletes will attend a familiarization session during which the researchers will provide detailed instructions on how to perform the intervention. During the main intervention phase, the first session will be supervised by the research team, while the remaining sessions will be carried out individually, at different times according to each athlete’s training schedule. Each group will randomly receive the BB music-based intervention program.

The intervention group will receive a complete BB music-based intervention program. The placebo group will receive the same music-based intervention program with the verbal guidance but without the binaural beats. The control group will listen only to the music track, with the same music background as the intervention and placebo groups.

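### Club athletes are individually randomised to three portable tracks and only website visits are counted, so cross-arm listening and comparison of tracks are possible and would go unseen

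*Protocol article*

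**What the plan says.** **Who is enrolled and how they are allocated (Protocol article, section 2.1).** Participants "will be recruited from collaborating sports clubs located in the Attica region of Greece", with team coaches helping to recruit. They are "athletes participating in open-skill sports, including football, basketball, volleyball, and handball", and "Athletes must be active members of their respective team with a frequency of engaging in sports 3–5 times per week". Allocation is by individual athlete: "Participants will be randomly assigned in a 1:1:1 ratio to one of three groups: the experimental group, the placebo group, or the control group", 18 per group. No club stratum is mentioned. The section also states: "Participants, outcome assessors, and statisticians will remain blinded to group allocation throughout the study".

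**What they receive (section 2.4).** The experimental track has music, verbal guidance and binaural beats. The placebo track has the same music and guidance without the beats. The control track has the music alone. On format: "BB is layered with background music and will be provided in MP3 format". Every athlete reaches the material through one website built for the study.

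**When and how they listen.** Section 2.2 describes the programme as "incorporated into the warm-up phase prior to each training session and official game". Section 2.4 says the research team supervises the first session, and that "the remaining sessions will be carried out individually, at different times according to each" athlete's training schedule. Athletes are told to sit in a quiet place with eyes closed, and delivery is by headphones.

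**How adherence is checked (section 2.4).** The researchers follow the frequency of athletes' visits to the website. No other check on what was heard is described.

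**The concern.** All the named sports are team sports, and eligible athletes are active team members. If several athletes from one club enrol, individual allocation will usually put them in different arms. They would then hold different audio files and meet at training several times a week. Two things could follow.

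- **Dilution.** A placebo athlete who uses a teammate's beats track, or the reverse, pulls the two arm means together. Beats versus placebo is the only comparison that isolates the beats from music and guidance, which section 5 names as a strength of the three-arm design.
- **Loss of blinding.** The music-only track lacks the spoken guidance that the other two carry. One comparison with a teammate could tell a control athlete which arm they are in. Kinesiophobia, one of the primary outcomes in the abstract, is self-reported and so open to that knowledge.

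The stated monitoring would detect neither. A visit count measures how often the site was opened. It does not say which track was played, and it misses any file passed on outside the site. If beats and placebo did not differ at the end, the trial could not say whether the beats have no effect or the arms heard each other's tracks.

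**Working it through.** **Step 1. Can teammates land in different arms?** The number of athletes per club is not given. Treating allocations as independent, the chance that k enrolled teammates span at least two arms is 1 − 3^(1−k). That is 1 − 1/3 = 67% for k = 2 and 1 − 1/9 = 89% for k = 3. This is opportunity for contamination, not contamination itself.

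**Step 2. Reproduce the plan's sample size.** Inputs from section 2.1 are f = 0.25, alpha 0.05, power 0.95, 3 groups, 3 time points, minimum N = 48, and dropout of about 10%. The correlation among repeated measures (ρ) is not stated. For the group-by-time interaction with sphericity:

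- λ = f² · N · m / (1 − ρ), with m = 3
- df1 = (3 − 1)(3 − 1) = 4; df2 = (48 − 3)(3 − 1) = 90

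With ρ = 0.55, λ = 0.0625 × 48 × 3 / 0.45 = 20.0 and power is 95.4%, so N = 48 is reproduced. With ρ = 0.50, λ = 18.0, power at 48 is 93.0%, and 52 would be needed (54 with equal groups). I use ρ = 0.55 because it returns the plan's figure. Dropout: 48 / 0.90 = 53.3, rounded up to 54, as stated. The target therefore allows for dropout only.

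**Step 3. Illustrate the cost of dilution.** The rate is not in the documents. Let c be the assumed fraction of the effect lost, so f becomes 0.25(1 − c) and λ is multiplied by (1 − c)².

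| c (assumed) | f | λ at N = 48, ρ = 0.55 | Power, ρ = 0.55 | Power, ρ = 0.50 | Completers for 95%, ρ = 0.55 |
|---|---|---|---|---|---|
| 0 | 0.250 | 20.0 | 95.4% | 93.0% | 48 |
| 10% | 0.225 | 16.2 | 89.9% | 86.2% | 60 |
| 20% | 0.200 | 12.8 | 80.8% | 75.9% | 75 |
| 30% | 0.175 | 9.8 | 68.0% | 62.7% | 96 |

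**Step 4. How to read the table.**

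- It shrinks the whole group-by-time effect by c. If only placebo athletes were contaminated, the three-arm test would lose less. With true effects (1, 0, 0) turning into (1, c, 0), the between-arm sum of squares falls by a factor of 1 − c + c², which is 0.91 at c = 10%, against 0.81 in the table.
- The beats-placebo difference itself would still fall to 1 − c.
- If a share s of both arms swapped tracks, that difference would fall to 1 − 2s. At s = 10%, 80% of the effect remains, and the same power needs 1 / 0.8² = 1.56 times the sample.
- Each case assumes that a contaminated athlete takes on the full effect of the other track. Trying a teammate's track once in a 20-session programme would do much less.

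**The case against.** The strongest reply is that this rests on silence. A journal article condenses the full protocol, and logins, download settings and instructions to athletes are details it may leave out. The site was built for this study alone, and counting each athlete's visits suggests that athletes are identified in some way. A familiarisation session is also planned, though what it says about sharing is not given. This stands. A reader might infer that nothing ties a track to its athlete, but the article does not show that. It shows only that the monitoring it describes is a visit count.

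Second, section 2.4 has athletes listening alone, at different times and in a quiet place, with headphones. Overhearing is therefore unlikely, and it would be wrong to describe listening as a shared team activity. What teammates share is the training or match that follows. Separate listening does not stop a file being passed on or tracks being discussed.

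Third, two stronger readings are tempting and fail:

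- Control athletes who hear the beats track do not shrink the beats-versus-placebo contrast, because they are not in it.
- Comparing tracks would not readily unblind beats against placebo. Those two share music and guidance, and noticing a difference does not say which is active. Only the music-only track is easily recognised.

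Fourth, section 5 already concedes that listening conditions in independent sessions may vary. That concerns the environment. It does not cover sharing or comparing tracks.

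**Conclusion.** The point holds as a risk that is possible and, with the monitoring described, unmeasured. It is not a demonstrated bias. Individual allocation among club athletes, three distinct tracks, MP3 supply, unsupervised sessions and a visit count together mean that cross-arm listening could occur without being detected. A null beats-versus-placebo result would then be ambiguous.

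The documents cannot fix the size. The drop from 95% to about 90%, 81% or 68% power depends on assumed losses of 10%, 20% and 30%, on ρ = 0.55, and on the loss applying to the whole effect. Joint enrolment of teammates is likely but not stated.

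A reader might infer that individual randomisation is itself the fault and that clubs should be randomised instead. The documents do not support that. With 54 athletes there would be few clusters, and any within-club correlation would cost power. The randomisation should stay. This is a cheap improvement to delivery and monitoring, not a flaw that invalidates the design.

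**What to change.** In section 2.4:

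1. State whether access is personal and limited to the allocated track. If it is not, set it so: stream the track without download, and log plays by athlete and track in place of a bare visit count.
2. Instruct athletes at the familiarisation session not to share or discuss their tracks.
3. At both post-baseline visits, ask whether the athlete heard another participant's track or used another binaural programme.
4. Record each athlete's club.
5. Report exposure to other arms' tracks by arm, alongside the intention-to-treat result, which remains primary.

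The cost is minor website work, one instruction and a few questions at visits already planned. The downside is that the trial may have to disclose some contamination. If access is already locked to the allocated track, one sentence settles item 1 and the rest still applies. Access control and the instruction only help while athletes are still listening, so they should be in place before the intervention starts.

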### 2.5. Statistical Analysis

Data will be summarized using descriptive statistical methods. Continuous variables will be presented as means and standard deviations, whereas categorical variables will be expressed as frequencies and percentages. Normality of continuous variables will be assessed using the Shapiro–Wilk test.

Baseline demographic, anthropometric, and clinical characteristics will be compared across the three study groups to assess baseline comparability. Continuous variables will be analyzed using one-way analysis of variance (ANOVA) or the Kruskal–Wallis test, as appropriate, whereas categorical variables will be compared using Pearson’s chi-square test or Fisher’s exact test. Ordinal variables will be analyzed using the chi-square test for trend where applicable. If clinically meaningful baseline imbalances are detected, adjusted analyses using mixed-design ANCOVA models will be conducted.

The primary analysis will follow the intention-to-treat principle, whereby all randomized participants will be analyzed in the groups to which they were originally allocated, regardless of adherence to the intervention protocol or study completion. Missing data will be examined before analysis by assessing the extent and pattern of missingness. Where appropriate, missing values will be handled using multiple imputation procedures, and sensitivity analyses will be performed to evaluate the robustness of the findings.

To investigate changes across the 4-week BB intervention period (Time factor) and differences among the three groups (experimental, placebo, and control), a mixed-design analysis of variance (ANOVA) will be performed. The assumptions of the mixed-design repeated-measures ANOVA, including normality of the model residuals, homogeneity of variances, and sphericity, will be assessed before analysis. This analysis will assess the main effects of Time (within-subjects factor) and Group (between-subjects factor), as well as their interaction [78]. When significant effects are identified, post hoc pairwise comparisons will be performed with appropriate adjustment for multiple comparisons. If clinically meaningful baseline imbalances are detected, adjusted analyses using mixed-design ANCOVA models will be conducted.

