Additional limitations include heterogeneity in injury characteristics, such as injury duration, severity, diagnosis, rehabilitation history, training load, and competitive level, all of which may influence recovery and intervention responsiveness. Although the inclusion of both male and female athletes enhances the generalizability of the study, the sample is not specifically powered to examine sex-specific effects. Therefore, any sex-related differences in psychological, autonomic, or fitness-related responses will be interpreted with caution and considered exploratory. Finally, environmental listening conditions during independently completed intervention sessions may not be fully controlled, potentially introducing variability in participants’ exposure to the auditory intervention.

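### In a trial pooling men and women, sex can enter the analysis only through a rule triggered by observed baseline imbalance; it should be a fixed, prespecified model term

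*Protocol article*

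**What the plan says.** Section 2.1 pools the sexes: "A total of 54 professional male and female athletes aged 18–25 years will be recruited". Allocation is equal: "Participants will be randomly assigned in a 1:1:1 ratio to one of three groups", with 18 per group. The method is given as "Randomization will be performed using a computer-generated random allocation sequence", prepared by an independent researcher and concealed in sealed envelopes. The article mentions neither stratification nor blocking nor minimisation by sex.

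Section 2.5 defines the main analysis as a mixed-design ANOVA with Time, Group and their interaction, followed by pairwise comparisons where effects are significant. Sex is not a factor. Baseline variables are compared across arms, with a chi-square or Fisher test for categorical ones. Then, stated twice: "If clinically meaningful baseline imbalances are detected, adjusted analyses using mixed-design ANCOVA models will be conducted". The section gives no threshold for that judgement and no list of the variables it covers.

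Section 5 acknowledges sex only as a question of subgroup effects: "the sample is not specifically powered to examine sex-specific effects". The Introduction lists sex among the intrinsic injury factors.

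**The concern.** Grip strength and VO2/kg can be expected to differ in level between men and women. With 18 per arm and no restriction by sex, the arms may by chance hold noticeably different numbers of women. Two things follow.

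- Raw arm means of these outcomes move with the sex mix. The Group main effect averages over all three visits, baseline included, so it carries that shift. So do pairwise comparisons of arm levels.
- Whether an analysis adjusted for sex exists at all depends on the allocation drawn and on a judgement made after the baseline data are seen. A known prognostic factor need not be left to such a rule.

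**Working it through.** **Inputs.** From section 2.1: 54 athletes, 18 per arm. Assumed, because the article gives no sex ratio: 9, 14, 18, 22 or 27 women. Assumed sex difference in grip strength and VO2/kg: d = 1.0 to 2.0 within-sex SD.

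**The plan's own figure.** Section 2.1 states "the minimum required sample size was estimated at 48 participants" and allows for about 10% dropout. 48 / 0.90 = 53.3, rounded up to 54, or 18 per arm, so the inflation reproduces. The 48 depends on a repeated-measures correlation that the article does not state: for the interaction at f = 0.25, power at N = 48 is 0.930 if the correlation is 0.5 and 0.954 if it is 0.55. This does not affect the present point, which needs only 18 per arm.

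**Chance imbalance.** With W women among 54 and no restriction by sex, the chance of a, b and c women in the three arms is

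P(a, b, c) = C(18,a) · C(18,b) · C(18,c) / C(54,W), with a + b + c = W.

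Summing over all splits, with gap = largest minus smallest count of women:

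| Women of 54 | Gap ≥ 3 | Gap ≥ 4 | Gap ≥ 5 | Gap ≥ 4, one given pair | Chi-square p < 0.05 |
|---|---|---|---|---|---|
| 27 | 65.4% | 46.6% | 31.5% | 24.7% | 3.4% |
| 22 | 69.3% | 47.2% | 27.4% | 23.9% | 4.7% |
| 18 | 62.1% | 42.5% | 27.1% | 22.0% | 7.7% |
| 14 | 63.2% | 39.2% | 19.6% | 18.7% | 3.4% |
| 9 | 46.7% | 25.9% | 11.7% | 11.9% | 2.9% |

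A gap of 3 is 3/18 = 17 percentage points; a gap of 4 is 4/18 = 22 points.

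**Effect on arm levels.** Shift in the raw contrast = (gap/18) × d. For a gap of 4: 4/18 × 1.0 = 0.22 SD and 4/18 × 2.0 = 0.44 SD. For scale, take the planned f = 0.25 as the spread of three arm means. The largest pairwise difference is then 0.25/√(2/9) = 0.53 SD if two arms coincide, or 0.25/√(1/6) = 0.61 SD if the means are equally spaced.

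**Effect on the interaction.** If sex adds a constant d to level, each arm mean contains d × (proportion of women) at every visit. Subtracting baseline removes it. Only a sex difference in change over time would remain.

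**What a sex term gains.** With a proportion p of women, sex adds v = p(1 − p)d² to a within-sex variance of 1, so its share of raw between-athlete variance is v/(1 + v).
- For 18 women (p = 1/3) and d = 1: 0.222/1.222 = 18%.
- For 27 women (p = 1/2) and d = 2: 1/2 = 50%.

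Once baseline is in the model, with within-sex correlation r between visits, adding sex multiplies the residual variance by (1 + r)(1 + v)/(1 + r + 2v). Taking r = 0.8 (assumed) and p = 1/2:
- d = 1: 1.8 × 1.25/2.3 = 0.978, a cut of about 2%.
- d = 2: 1.8 × 2/3.8 = 0.947, a cut of about 5%.

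Across r = 0.7 to 0.9 the cut runs from about 1% (r = 0.9, d = 1: 1.9 × 1.25/2.4 = 0.990) to about 8% (r = 0.7, d = 2: 1.7 × 2/3.7 = 0.919).

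**The case against.** The case on the other side is substantial, and most of it stands.

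- **Silence is not an error.** The article is condensed, and the full protocol may stratify. A reader might infer that randomisation is known to be unrestricted by sex; the text does not say so. Even if it were, unstratified allocation of 54 athletes is valid.
- **A sex gap need not set off the adjustment.** A reader might infer that a marked gap is likely and would by itself trigger the ANCOVA. A gap of 4 or more stays below 50% in every scenario, and for one given pair of arms it is 12–25%. The trigger is undefined and does not name sex. If the chi-square comparison in section 2.5 were the guide, it would flag sex in only about 3–8% of draws. The text supports could, not would.
- **No bias on average.** A reader might infer that chance imbalance biases the comparison or inflates type I error. It does neither on average; the 0.22–0.44 SD shift is conditional on an unlucky draw.
- **Replacement is not stated.** Section 2.5 says that adjusted analyses will be run, not that they supersede the unadjusted ones.
- **Limited reach.** The Abstract lists handgrip strength and VO2max as secondary. Nothing here shows a sex effect on the primary outcomes (TSK-17, SSR, HRV), and the test of differential change is largely protected.
- **Stratification is not free.** With 20 women and 34 men, incomplete final blocks of 6 could leave arms of 20, 18 and 16.

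What the objection leaves untouched is the stated rule: section 2.5 makes adjustment depend on the observed data under an undefined criterion, and the main model has no sex term although it tests a Group main effect and allows pairwise arm comparisons.

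**Conclusion.** The point holds as a low-severity improvement to the analysis. A gap of at least 3 women between two of the arms has a chance of about 47–69%, and of at least 4 about 26–47%, assuming 9 to 27 women and no restriction by sex. Such a gap could prompt the conditional adjustment. At an assumed sex difference of 1–2 SD, a gap of 4 shifts raw arm contrasts in grip strength and VO2/kg by 0.22–0.44 SD. The documents give neither the sex ratio nor the size of the sex difference.

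The consequence concerns precision, interpretability and analytic freedom in level comparisons of secondary outcomes. It is not a threat to the validity of the randomised comparison or of the Group × Time test.

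**What to change.** For sex, replace the conditional rule with a fixed one: enter sex as a prespecified main effect in every model, whatever imbalance is observed. Leave out a Group × Sex term from these models, so that sex-specific effects stay exploratory as section 5 intends. The cost is one model term: between-athlete error degrees of freedom fall from 54 − 3 = 51 to 50. This can be adopted even if enrolment has begun, provided it is fixed before outcome data are examined by arm.

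Optionally, if enrolment has not begun and the full protocol does not already do so, generate a separate allocation list and envelope set for each sex in small permuted blocks. Blocks of 3 cap the between-arm gap within each sex at 1, and blocks of 6 at 2. The price is a second list and arms that may not be exactly 18 each. If the full protocol already stratifies, one sentence in section 2.1 should say so.

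This change settles sex only. For other baseline variables the conditional rule in section 2.5 would still need named covariates or a defined threshold.
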